### Sample size

Based on a comparison of the percentages of patients with a non union at 12 weeks following treatment, it is estimated that 141 patients will be required in each treatment group to detect at least a reduction in percentages from 15% [6] to 5% non union with 80% power and a significance level of 5% [25]. A 4% non union rate has been quoted in the literature [26], however for the purposes of this calculation we have used a 5% as a maximum acceptable clinical failure rate. By randomising 300 patients (150 per group) the study will be adequately powered with allowance for loss to followup. Recruitment of 300 subjects will also ensure at least 80% power to detect clinically important effects for secondary outcomes. For the DASH score this will allow detection of a 3.3 point difference in mean scores with a significance level of 5% (assuming a standard deviation of 10) [20]. For the Constant-Murley score a 5 point difference in mean scores will be detectable at a 5% significance level (assuming a standard deviation of 14.5) [19]. Calculations have assumed approximate Normality of the scores [25].

It is estimated that 13 patients per month will be recruited to the study. This would lead to a total period of recruitment for the trial of 23 months.

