#### Recruitment

Patients will be identified at attendance to the accident and emergency department at each hospital. They will be referred to fracture clinic, as this is the usual practice, and identified as eligible for the trial by the consultant surgeon in charge of the clinic.

It is estimated that in each centre approximately 2 patients per month will meet the inclusion criteria. It is also estimated that 80% of these patients will consent to be involved in the trial. Loss to follow-up will be small until 3 months, though for final follow-up and assessment is estimated a further 10% may be lost to follow-up.

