The DASH score [20] is a patient completed subjective score with 30 analogue scale responses producing a score between 0 and 100 points. The DASH score is a standardized questionnaire that assesses the symptoms and functional status in people with different upper extremity musculoskeletal disorders. The questionnaire consists of three sections: Symptoms, Sport and Music, Work. The first section is composed by 30 items and evaluates symptoms and functional status at the level of disability. The second and third sections are an optional module of four items for Sport and Music and four items for Work. Each item is scored with a five point scale: 1 = no difficulty; 2 = mild difficulty; 3 = moderate difficulty; 4 = severe difficulty; 5 = unable. The result of each module is summed and transformed to obtain the DASH score ranging, for each section, from 0 (no disability) to 100 (severe disability). Relatively to Internal Consistency the DASH has shown in multiple tests to have a high Cronbach's alpha (0.97); the responsiveness of the questionnaire (to self-rated or expected change) was comparable with or better than that of the joint-specific measures in the whole group and in each region [23].

An independent physiotherapy practitioner not involved in patient's surgical care or rehabilitation program will administer both assessment tools. There will a different examinator in each centre, who will be trained for the purpose of this study. The Constant score will be performed in a standardized way, using the same dynamometer in all the centres.

In the event of a patient developing a non-union at 12 weeks or more, he/she will exit the trial and be offered surgical management. Data regarding treatment offered and pursued will be collected.

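### The floor of 80% power claimed for the secondary outcomes does not hold for DASH at 9 months: the protocol's own 10% loss leaves about 77%

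*Protocol article*

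**What the plan says.** The Sample size section of the protocol article derives 141 patients per group for the primary outcome (non-union of 15% versus 5%, 80% power, 5% significance) and rounds up: "By randomising 300 patients (150 per group) the study will be adequately powered with allowance for loss to followup". It then extends the claim: "Recruitment of 300 subjects will also ensure at least 80% power to detect clinically important effects for secondary outcomes". The supporting figures are "For the DASH score this will allow detection of a 3.3 point difference in mean scores" ("assuming a standard deviation of 10") and "For the Constant-Murley score a 5 point difference in mean scores will be detectable at a 5% significance level", the latter with a standard deviation of 14.5.

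The power claim carries no time point. Endpoints and Data Analysis both define the two scores as outcomes at 3 and at 9 months, so it covers both.

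Two other places bear on how many patients can be scored at 9 months. Recruitment expects little loss up to 3 months, but says that "for final follow-up and assessment is estimated a further 10% may be lost to follow-up". Assessment says that a patient with a non-union at 12 weeks or later "he/she will exit the trial and be offered surgical management", and that data on the treatment offered and pursued will be collected. It does not mention 9-month scores for these patients. Data Analysis says that every analysis follows the intention-to-treat principle.

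**The concern.** The secondary power figures come out above 80% when all 150 patients per arm are scored. For DASH the margin is thin: about 145 of 150 are needed. The document itself forecasts a larger loss than that by the final visit, so the floor and the attrition estimate cannot both be right for DASH at 9 months.

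Nine months is the only functional assessment after the 3-month visit. The protocol treats the stated differences as clinically important, so a null 9-month DASH result would be read against a promised power of 80% or more, when the chance of missing a true 3.3-point difference is about 23% on the protocol's own loss figure.

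**Working it through.** **Inputs.** Sample size: 150 per arm; 5% significance; DASH difference 3.3, SD 10; Constant-Murley difference 5, SD 14.5; planning non-union rates 15% and 5%. Recruitment: a further 10% loss at final follow-up. The number of sides of the test is not stated. Two-sided is assumed because it reproduces the primary figure: [1.96 × √(2 × 0.10 × 0.90) + 0.8416 × √(0.15 × 0.85 + 0.05 × 0.95)]² / 0.10² = (0.8316 + 0.3521)² / 0.01 ≈ 140.1, so 141 per group.

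**Formulas** (normal approximation, unadjusted difference in means):

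- Patients per arm for 80% power: n = 2 × (1.96 + 0.8416)² × (SD/difference)²
- Power: Φ(difference/SE − 1.96), with SE = SD × √(1/n₁ + 1/n₂)
- Difference detectable with 80% power: 2.8016 × SE

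**Step 1: reproduce the plan's claim at 150 per arm.**

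- DASH: SE = 10 × √(2/150) = 1.155; 3.3/1.155 − 1.96 = 0.898; power 81.5%.
- Constant-Murley: SE = 14.5 × √(2/150) = 1.674; 5/1.674 − 1.96 = 1.026; power 84.8%.

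The claim is correct for 300 complete patients.

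**Step 2: how much loss it tolerates.**

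- DASH: 2 × 7.849 × (10/3.3)² = 144.2, so 145 per arm. The slack is 5 of 150, or 3.3%.
- Constant-Murley: 2 × 7.849 × (14.5/5)² = 132.0, so 133 per arm. The slack is 17 of 150, or 11.3%.

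**Step 3: apply the stated 10% loss.** 150 × 0.9 = 135 per arm. This is an upper limit, since the 10% comes on top of a small unquantified loss before 3 months.

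- DASH: SE = 10 × √(2/135) = 1.217; 3.3/1.217 − 1.96 = 0.751; power 77.4%; detectable difference 2.8016 × 1.217 = 3.41.
- Constant-Murley: SE = 1.765; 5/1.765 − 1.96 = 0.873; power 80.9%; detectable difference 4.94.

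**Step 4 (conditional): non-union exits not scored, at 15% and 5%, plus 10% loss.** 150 × 0.85 × 0.9 = 114.75 and 150 × 0.95 × 0.9 = 128.25.

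- DASH: SE = 10 × √(1/114.75 + 1/128.25) = 1.285; 3.3/1.285 − 1.96 = 0.608; power 72.9%; detectable difference 3.60.
- Constant-Murley: SE = 1.863; 5/1.863 − 1.96 = 0.723; power 76.5%; detectable difference 5.22.

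**Summary**, with the noncentral t result in brackets:

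| Evaluable per arm | DASH, 3.3 points | Constant-Murley, 5 points |
|---|---|---|
| 150 v 150 | 81.5% (81.3%) | 84.8% (84.5%) |
| 135 v 135 | 77.4% (77.1%) | 80.9% (80.6%) |
| 114.75 v 128.25 (conditional) | 72.9% (72.5%) | 76.5% (76.2%) |

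The two methods agree to within half a percentage point.

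**The case against.** **The unconditional shortfall is small.** This stands. With the stated loss alone, Constant-Murley meets its claim. DASH misses by about 3 points of power, and its detectable difference moves by about 0.1 point on a 0 to 100 scale. A standard deviation of 3.3/(2.8016 × 0.1217) ≈ 9.7 instead of 10 would restore 80%. That limits the weight of the point, but a stated floor should still agree with the document's own attrition figure.

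**The planned analysis is analysis of covariance, which can recover power.** This stands in part. The Sample size section takes no credit for it and the document gives no correlation, so any gain is an assumption. A correlation of about 0.29 would bring Constant-Murley back to 80% even with exits and loss, and that score is measured on both arms. DASH with 10% loss would need about 0.25, but no other-limb or pre-injury DASH measurement is described. The gain cannot be credited to DASH.

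**No time point is attached to the claim, and at 3 months it holds.** This is true for 3 months, provided about 145 per arm are scored. But the claim is made for the secondary outcomes as a whole, and these include 9 months.

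**Stronger readings that the document does not support.**

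- A reader might take 73% and 76% as the design's actual 9-month power. Those figures need two assumptions: that leaving the trial means no 9-month score, and that exits occur at 15% and 5%. Assessment does not say the first outright, and intention-to-treat in Data Analysis points the other way. The second borrows planning values for the primary outcome. Moreover, Endpoints defines non-union radiographically while Adverse Events or Complications also requires clinical signs, and the document does not say which definition triggers exit.
- A reader might start from 141 per arm at 3 months and reach about 70% and 74% after exits and loss. But 141 is a required size, not a forecast of retention, and Recruitment expects little loss by then.

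**Conclusion.** The statement is wrong as written for DASH at 9 months. With the protocol's own further 10% loss, at most 135 per arm are evaluable and power for 3.3 points is about 77%, not at least 80%. This rests on a two-sided 5% test, the stated standard deviation of 10 and an unadjusted comparison, which is the basis on which the plan's figures reproduce. Under the same loss the Constant-Murley claim holds at about 81%, and at 3 months both claims stand.

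Power of about 73% (DASH) and 76% (Constant-Murley) at 9 months follows only if patients who exit with a non-union are not scored and exits match 15% and 5%. The document leaves that open, and the exit wording and the intention-to-treat statement must be reconciled.

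The effect is modest and limited to secondary outcomes; the primary sample size is not affected. A null DASH result would not exclude 3.3 points at 80% power either, so the correction is to the accuracy of a stated property rather than to how the trial is run.

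**What to change.** Restate secondary power in the Sample size section by time point, with the loss assumption shown:

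- **3 months:** 3.3 DASH points and 5 Constant-Murley points stand.
- **9 months, 10% loss (135 per arm):** 80% power for about 3.4 DASH points, or state about 77% for 3.3. The 5 Constant-Murley points stand.
- **9 months, only if exited patients are not scored:** about 3.6 DASH and 5.2 Constant-Murley points at 80% power.

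Reconcile the exit statement in Assessment with the intention-to-treat statement in Data Analysis, so that it is clear whether exited patients contribute 9-month scores and which 9-month line applies.

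No patients need be added. Covering the 10% loss for DASH alone would take 145/0.9 = 161.1, so 162 per group or 324 in total, which a 3-point shortfall on a secondary outcome does not justify. The cost is a slightly less favourable stated figure.

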### Data Analysis

The success of randomisation will be made in a visual comparison of the baseline characteristics of those randomised to the two groups: centre, age, gender, side of injury, mechanism of injury, fracture classification [21] and ASA grade.

The representativeness of the groups randomised to the trial will be examined by comparing their baseline characteristics with those who were eligible but refused to participate.

The primary outcome is the rate of non union in each group at 3 months. Secondary outcomes are Constant-Murley and DASH scores at 3 months and 9 months following injury.

All of the analyses will use the intention-to-treat principle. The primary outcome will be compared between the conservative and operative groups using generalised linear regression models both unadjusted and adjusted for centre (the stratification factor), age, fracture classification and ASA grade. Estimates of the difference in proportions and odds ratio with associated 95% confidence intervals will be obtained.

The Constant-Murley and DASH outcomes will be compared between groups using analysis of covariance. This will allow for a baseline score as suggested through measurements recorded for the other normal limb. The assumptions of this approach will be checked using summary information and graphs. If assumptions are not met, appropriate data transform or non parametric methods will be considered. Multiple regression models will be used to investigate the intervention effect after adjustment for centre, age, fracture classification and ASA grade.

Where outcome data are missing, a check of the characteristics of those with and without the outcome of interest will be carried out to ensure that missing data have not biased a comparison based on complete data. All analyses will be carried out using Stata.

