#### Randomisation

Randomisation lists will be computer generated. Lists will be stratified by centre and blocked to ensure similar numbers of patients are allocated to the treatment groups within each centre. Allocations will be concealed in sequentially numbered opaque envelopes held at each site. 1 envelope will be opened for each patient. Eligible patients will be provided with a patient information sheet and consented using a trial consent form prior to randomisation.

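### The named comparison of the functional scores leaves out centre, the randomisation stratum, and no single model is stated to hold both centre and the other-limb score

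*Protocol article*

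**What the plan says.** All passages are in the protocol article.

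- Data Analysis, the named comparison: "The Constant-Murley and DASH outcomes will be compared between groups using analysis of covariance". On its covariate: "This will allow for a baseline score as suggested through measurements recorded for the other normal limb". No other covariate is given for this model.
- Data Analysis, the further model: "Multiple regression models will be used to investigate the intervention effect after adjustment for centre, age, fracture classification and ASA grade". The other-limb score is not in that list. The section does not say that it is dropped, nor which of the two models leads.
- Randomisation: "Lists will be stratified by centre and blocked to ensure similar numbers of patients are allocated to the treatment groups within each centre". Data Analysis itself identifies centre as the stratification factor when it describes the primary-outcome models.
- Assessment, on the scoring: "There will a different examinator in each centre, who will be trained for the purpose of this study". For the Constant score it adds: "The Constant score will be performed in a standardized way, using the same dynamometer in all the centres".
- Assessment describes Constant-Murley as taken on both arms. It describes DASH as a questionnaire that the patient completes, with no second-limb score.

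**The concern.** Blocking within centre balances the arms inside each centre, so differences between centres largely cancel out of the treatment contrast. A model without centre does not know this. It leaves the between-centre variation in its residual and reports a standard error larger than the true sampling variation. Confidence intervals are then somewhat too wide and the test rejects less often than its nominal 5%.

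Having a different examiner at each centre is one plausible source of such variation. The other-limb score might absorb part of it for Constant-Murley. For DASH no other-limb score is described, so the analysis of covariance has no described covariate at all.

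The plan also yields two estimates per score and time-point without ranking them, although one model could use both the stratum and the other-limb score. At stake is a modest amount of precision on the secondary outcomes.

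**Working it through.** **Inputs from the article.** 300 patients, 150 per group; DASH difference 3.3, SD 10; Constant-Murley difference 5, SD 14.5; 5% significance, taken as two-sided (Sample size). A further 10% lost by final follow-up (Recruitment), so 150 × 0.9 = 135 per group. Four sites recruiting and four planned, so 8 centres (Trial timeline).

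**Assumed, not in the article.** c, the share of score variance due to centre: 0.05–0.10, with 0.02 as a low case. r, the correlation between the injured- and other-limb Constant-Murley scores: 0.3–0.5.

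**1. The plan's own figures.** 15% versus 5% at 80% power gives 141 per group (pooled variance, no continuity correction), as stated. For the scores, SE = SD × √(2/n) and power = Φ(difference/SE − 1.96).
- DASH, n = 150: SE = 10 × √(2/150) = 1.155; 3.3/1.155 = 2.858; power 81.5%.
- Constant-Murley, n = 150: SE = 1.674; 5/1.674 = 2.986; power 84.8%.

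The stated power of at least 80% is reproduced at 150 per group. These calculations use no covariate.

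**2. After 10% loss, with no centre effect.** DASH, n = 135: SE = 1.217; 3.3/1.217 = 2.711; power 77.4%. Constant-Murley: 80.9%.

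**3. Effect of leaving out centre.** With balanced allocation within centres, the true SE is the reported SE × √(1 − c). The reported SE is therefore too large by the factor 1/√(1 − c), and the actual type I error is 2 × [1 − Φ(1.96/√(1 − c))].

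| c | SE factor | Actual type I error |
|---|---|---|
| 0.02 | 1.010 | 4.8% |
| 0.05 | 1.026 | 4.4% |
| 0.10 | 1.054 | 3.9% |

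**4. DASH power at 135 per group.** Without centre: Φ((2.711 − 1.96)/√(1 − c)). With centre: Φ(2.711/√(1 − c) − 1.96).

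| c | Without centre | With centre |
|---|---|---|
| 0.02 | 77.6% | 78.2% |
| 0.05 | 78.0% | 79.4% |
| 0.10 | 78.6% | 81.5% |

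A simulation with 8 uneven centres and 270 patients agrees. At c = 0.05 and 0.10 it gives type I error of 4.4% and 4.2% without centre. Power is 77.8% and 79.3% without centre, and 79.2% and 82.4% with it.

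**5. Constant-Murley: adding centre to the other-limb model.** Take residual SD as 14.5 × √(1 − r²) without centre and 14.5 × √(1 − r² − c) with it, which treats the two contributions as separate.
- 135 per group, r = 0.3: 84.4% without centre; 85.2%, 86.3% and 88.3% with centre at c = 0.02, 0.05 and 0.10.
- 135 per group, r = 0.5: 90.5% without centre; 91.2%, 92.3% and 94.0% with it.
- 150 per group: gains of 0.6 to 3.4 points.

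The largest gain is 88.3 − 84.4 = 3.9 points. It is an upper limit, because 84.4% takes the reported SE as the true one. With the formula of step 4, power without centre at r = 0.3 and c = 0.10 is Φ((2.833/√0.91 − 1.96)/√(0.81/0.91)) = Φ(1.07) = 85.8%, and the gain is about 2.5 points. If the same examiner's effect enters both limbs, the other-limb score already carries much of it: the simulation then gives 86–94% for the covariance model and 87–94% with centre added, a gain of at most about 1 point.

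**The case against.** The strongest reply is that centre adjustment is already planned. For DASH, the further regression has exactly the covariates proposed here. The section follows the pattern used for the primary outcome, a simpler analysis and then an adjusted one, and reporting both is ordinary practice. A condensed article may also leave the full covariate list to the analysis plan. All of this stands, and it keeps the severity low. It does not remove the point, because the comparison that the article does name is unstratified although the randomisation was stratified, and nothing ranks the adjusted model above it.

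The size can also be challenged. No between-centre variance is given, examiners are trained, the dynamometer is common to all centres, and patients complete DASH themselves. This stands too: at c = 0.02 the DASH difference is under 1 point of power (77.6% against 78.2%).

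Four stronger readings are tempting but unsupported.

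- A reader might infer that neither analysis uses the data collected. In fact the analysis of covariance uses the other-limb score and the regression uses centre. What is true is that neither is stated to use both.
- A reader might infer that the regression drops the other-limb score for Constant-Murley. The article does not say so. The sentence follows the analysis of covariance and can be read as extending it, so a power loss from a model without the other limb cannot be charged to the plan.
- A reader might infer bias or excess false positives. Allocation is balanced within centre and the error is in the conservative direction.
- A reader might blame DASH power below 80% on the missing centre term. Step 2 gives 77.4% at 135 per group with no centre effect, so attrition is the main cause.

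**Conclusion.** The point holds as a low-severity improvement to the analysis of the secondary outcomes. The named comparison of Constant-Murley and DASH omits the randomisation stratum, no single model is stated to combine centre with the other-limb score, and the lead model is not identified. There is no bias.

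Under the assumption that centre explains 5–10% of score variance, the cost to DASH at 135 per arm is about 1.4 to 3 points of power, with an interval about 3–5% wider than it need be. For Constant-Murley the cost relative to the covariance model is about 1 point if the examiner's effect is common to both limbs, and at most about 4 points if it is not. All these sizes scale with the assumed centre share and become negligible if that share is small.

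**What to change.** For each score and each time-point (3 and 9 months), state one main model: treatment, centre, age, fracture classification and ASA grade, with the other-limb score added for Constant-Murley only. Report the model without centre as supportive.

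The cost is a sentence or two of wording. All covariates are already collected. With 8 centres, two fracture classes and three ASA grades, the added terms use 7 + 1 + 2 degrees of freedom plus 1 for age. That is 11 of roughly 270, which the planned regression spends already.

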#### Trial timeline

Following a successful initial application for a British Society of Elbow and Shoulder Surgery primer grant, a period of 1 year for trial preparation, obtaining ethics approval, and Research and Development approval, a 6 month period establishing and piloting of all trial materials and processes was commenced at the Royal Free Hospital in December 2007, the official start date for general recruitment was July 2008. The award of a BUPA foundation grant allowed the appointment of a dedicated researcher in 2010 and the subsequently inclusion on National Institute of Health Research portfolio of clinical trials has allowed expansion of the trial sites. Currently there are 4 sites recruiting, and 4 further sites are planned, 2 of which have approval in place. The further planned recruitment period is 18 months, and completion of follow-up 9 months later. Study completion, which includes submission of the draft trial report to the funders for publication is scheduled for December 2012. The date of registration of the trial is 07/09/2006. The date the first patient was recruited is 18/12/2007.

